## Perspectives

The Svendborg City Council has granted generous resources to educate the staff; the staff at the preschools is eager to participate; the preschool teachers have contributed to the design of the intervention, ensuring a sense of ownership and involvement; and there is experience with conducting large, cluster randomised controlled trials in the Municipality. Therefore, the conditions for implementation of the intervention in the preschools are optimal. Consequently, if we cannot show an improvement in the children’s motor skills using this framework, further allocation of resources to programs to improve motor development in preschools should probably be discontinued.

On the other hand, if the intervention does succeed, the program can easily be applied in other Danish municipalities due to the design, where each preschool applies the intervention principles in a way to suit their individual conditions regarding physical environment, staffing, etc.

Finally, if the intervention improves motor competence in the children with the highest need for improvement, targeted interventions could be considered if, in some settings, prioritizing of resources is necessary.

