### Variables

*Primary outcome:*

Motor skills as assessed by the MovementABC-2 (as described in the main protocol) at the 18 month follow-up (spring 2018). At this point, the children will have received the intervention for 12 months after a six months phase-in period.

*Secondary outcomes:*

Child’s perceived physical competence

The perceived motor competence relating to everyday activities will be measured by the Perceived Physical Competence (PPC) subscale of Harter and Pike’s Pictorial Scale of Perceived Competence and Social Acceptance (PSPCSA) for preschool- and kindergarten-age children (4 to 7 years)(5). The PPC subscale assesses the children’s self-perceptions related to their ability to run, hop, swing, climb, tie shoelaces, and skip. On each pictorial plate, two pictures will be displayed side by side; one picture depicts a child who is competent in a particular task, and the other depicts a child who is not competent. The child selects the picture that is most like him/herself. Then, the child focuses on the selected picture and indicates whether

(s)he is ‘‘a little bit like’’ the child in the picture or ‘‘a lot like’’ the child in the picture. The range of scores for each item on the subscale is 1 (low competence) to 4 (high competence). The instrument has an internal consistency for the individual PPC subscale for preschool children of 0.62 (5). The assessment of the PPC subscale takes around 5 minutes.

Parent-perceived motor competence

The rating of parents’ perception of their child’s athletic coordination compared to other children of the same age has often been related to preschool-age children´s actual physical activity (9-11). An often used question for this assessment is “Compared with other children of the same age and sex, how would you describe your child’s level of athletic coordination?” with a response on a 5-point Likert scale, from 1 (much less coordinated) to 5 (much more coordinated) (10, 11). This question will be included in the parental baseline questionnaire and also mailed to the parents at the time of the last follow up before the child leaves preschool.

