## Analyses of effect

Simple univariate statistics will be used to describe the outcomes and covariates by preschool. Bivariate analysis adjusted for the design effect will be done to determine if there were any imbalances in the baseline covariates among the two groups.

Multilevel linear regression models will be constructed to assess the effectiveness of the intervention on motor skill performance. The baseline value of the outcome variable, time since baseline, intervention group and any imbalanced covariates will be added to the model along with preschool and socioeconomic status of the area as random effects. The interaction between preschool and intervention group will be tested. The assumptions for the models will be checked.

Multilevel ordinal regression models will be constructed to assess the effectiveness of the intervention on the parents’ perception of their child’s motor competence. The baseline value of the parents’ perception, time since baseline, intervention group and imbalanced covariates will be independent variables. The school and socioeconomic status of the area will be entered as random effects and the interaction between school and intervention will be tested. The model’s assumptions will be tested.

The above analyses will be repeated on a subsample of children who were considered to have a ‘poor’ level of motor competence at baseline.

An analysis will be conducted to determine if the children who dropped out of the study were different from those who remained, based on the baseline values of the outcome variables and the covariates.

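### WP 1 Perspectives treats failure to show an improvement as grounds for ending preschool motor programmes in general, without asking whether a worthwhile benefit has been ruled out

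*Protocol*

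**What the plan says.** WP 1, Perspectives, lists the council's funding of staff education, staff willingness and involvement in the design, and local experience with large cluster trials. From these it concludes that "the conditions for implementation of the intervention in the preschools are optimal". It then draws a consequence: should the trial be unable to show improved motor skills, "further allocation of resources to programs to improve motor development in preschools should probably be discontinued". The same section says that each preschool adapts the principles to its own circumstances. It also leaves room for targeted programmes if the children with the greatest need improve.

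The result in question is the primary outcome under WP 1, Variables: MovementABC-2 motor skills at the 18-month follow-up. Under WP 1, Analyses of effect, "Multilevel linear regression models will be constructed to assess the effectiveness of the intervention on motor skill performance", with terms for baseline value, time, group and imbalanced covariates, "along with preschool and socioeconomic status of the area as random effects". That section attaches no action to any result. Neither it nor Perspectives mentions a confidence-interval criterion, a margin or a smallest worthwhile difference.

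WP 2, Background, says that even efficient efforts will not have significant impact if they are implemented with insufficient quality. WP 2, Variables, sets out to establish whether delivery went as planned and, if not, why.

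**The concern.** Failing to show a benefit and showing that there is no worthwhile benefit are different findings. The first can arise from chance, limited precision or uneven delivery. The second needs an interval estimate narrow enough to exclude the smallest benefit anyone would pay for. The Perspectives sentence moves from the first to a conclusion that needs the second.

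It also widens the target. The trial tests one programme, adapted locally by each preschool, in one municipality. The conclusion covers preschool motor programmes as a class.

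At stake is what a null primary result may be used to say. Among the WP 1 sections this is the only stated consequence of such a result, and it concerns public funding. If quoted as it stands after an imprecise null result, it would support withdrawing resources on evidence that does not bear that weight.

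**Working it through.** **Reproduction.** There is no figure to reproduce. This file gives no sample size, significance level, power, target effect, standard deviation, intracluster correlation or margin for WP 1; it refers to a main protocol that is not at hand.

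**Step 1: the inference against its stated ground.** Good implementation conditions, if they hold, remove one explanation for a null result. They do not remove sampling error, and the sentence mentions neither power nor precision.

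**Step 2: the inference against the rest of the file.**
- WP 2 treats implementation quality as something to be measured, because poor quality can produce a null result. WP 1 Perspectives takes it as settled in advance.
- Local adaptation, and the planned test of a preschool-by-intervention interaction, both allow for delivery or effect to vary between preschools. That could dilute an average effect.
- WP 1 plans to repeat the analysis in children with poor motor competence at baseline, and Perspectives would consider targeted programmes if the neediest children improve. An overall null result with benefit in that group would call up both statements, and nothing says which applies.
- WP 1, Background, cites randomised trials indicating that preschool interventions can improve motor skills, and WP 3, Background, describes several as effective. One null result for one programme would not overturn these for the whole class.

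**Step 3: illustration of size.** Assumptions: normal approximation, two-sided 5% level, design power of 80% or 90% for some target effect, and a realised standard error equal to the planned one.

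Expected z when the target effect is real = 1.960 + z(power):
- 80% power: 1.960 + 0.842 = 2.802
- 90% power: 1.960 + 1.282 = 3.242

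Probability of missing a real target effect = 1 − Φ(expected z − 1.960):
- 80% power: 1 − Φ(0.842) = 0.20
- 90% power: 1 − Φ(1.282) = 0.10

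Upper 95% limit as a multiple of the target effect = (observed z + 1.960) / (1.960 + z(power)):

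| Observed z | 80% power | 90% power |
|---|---|---|
| 1.0 | 2.960 / 2.802 = 1.06 | 2.960 / 3.242 = 0.91 |
| 1.95 | 3.910 / 2.802 = 1.40 | 3.910 / 3.242 = 1.21 |

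The upper limit equals the target when observed z = z(power). So a null result with z between 0.84 and 1.96 (80% power), or between 1.28 and 1.96 (90% power), still includes the full target effect. Below those values the interval excludes it. Null results are therefore of two kinds, and the Perspectives sentence does not separate them.

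**The case against.** The strongest reply is that this is discussion text. It stands under Perspectives, says only that resources should probably stop, and names no test, p-value or significance level. Removing it would leave the primary outcome and the model unchanged, and nothing in the analysis section prevents interval reporting. It can be read as a pragmatic view: if a programme does not work under the best local conditions, further spending is hard to defend. WP 2 will examine fidelity, and the section keeps targeted programmes open.

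Most of this stands as a limit on the point. A reader might infer a formal decision rule driven by non-significance, or a claim that a null result proves no benefit. The text supports neither.

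A reader might also calculate how often the trial would miss effects smaller than the target. Under the same assumptions, the figures are 44% and 71% at three quarters and half of the target with 80% power, and 32% and 63% with 90% power. These do not measure wrongly abandoned benefit. If the sample-size difference is also the smallest worthwhile one, such effects fall below it. What remains is the ordinary 10% to 20% type II error of any trial with that power.

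The reply does not rescue the inference. A hedge on the conclusion does not supply the missing evidence about precision, favourable conditions do not exclude sampling error, and WP 2 is not linked to the sentence. The extension to all such programmes is unanswered.

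**Conclusion.** The point holds as a correction to a stated interpretation. WP 1 Perspectives treats inability to show improvement as evidence that worthwhile benefit is absent, and generalises it beyond the programme tested, although WP 2 names another cause of a null result. This does not depend on any power figure, since high power alone does not turn every null result into evidence of no benefit.

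The figures are illustrative and rest on an assumed level, assumed power and the planned precision being achieved: a real target effect is missed in 20% or 10% of trials, and at observed z = 1.0 the interval reaches about 1.06 or 0.91 times the target. A reader might conclude that the trial is underpowered. That cannot be said, because the main protocol with the sample-size reasoning is not shown. No estimate or model is affected, only what may be concluded from a null primary result.

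**What to change.** Replace the sentence in WP 1, Perspectives, with about two sentences to this effect: the trial counts against this programme only if the 95% confidence interval for the 18-month MovementABC-2 difference excludes a prespecified smallest worthwhile difference and the WP 2 findings show adequate implementation. Otherwise a null result is reported as inconclusive. Either way, the conclusion is confined to this programme.

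The margin has to be named before the results are known. The sample-size difference in the main protocol should serve only if it was judged the smallest worthwhile one; if it was chosen on other grounds, a separate margin is needed. The implementation condition matters because a poorly delivered programme could also give a narrow interval that excludes the margin.

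The change needs no new data collection, sample size or analysis model. Its cost is that a null result will support a less decisive statement.

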# WP 2: Process Evaluation

## Background

The rationale for including a process evaluation is that it creates the possibility to gain insight into what happens in local implementation processes. Even the most efficient efforts will, in practice, not yield signifi- cant impacts if they are not implemented with sufficient quality. The intervention to improve children´s motor skills is described in general in Appendix 2. It is up to local stakeholders to interpret the content in order to further operationalize various key components and thus be able to implement the intervention (1).

Overall, the process evaluation builds on the work of Michael Q. Patton, which deals with so-called utilization-focused evaluation. This approach enables the monitoring of activities and outputs to deliver continuous and solid feedback to those directly involved in the intervention and other key stakeholders.1 In later stages, the process evaluation will contribute to generating information about intervention dose and quality, e.g. dose-delivered, dose-received, consistency, appeal and fidelity.

The process evaluation will be guided by the RE-AIM framework (2). This ensures a holistic assessment of intervention impacts - focusing not solely on effectiveness, but also on the process of delivery and how, and to what degree, the main intervention components are institutionalized. For more than fifteen years, RE-AIM has been widely used to enhance the quality, speed, and public health impact of efforts to translate research into practice.

## Objective

To assess the implementation aspects of the intervention to improve motor skills.

## Variables

The RE-AIM framework consists of five fundamental questions:

**Reach:** How many in the overall target group can and are actually willing to participate in the intervention?

**Efficacy:** What kind of main and broader effects are to be expected? Information on the positive and negative effects (intentional or not) of an intervention is included.

**Adoption – setting level:** How many potential settings are willing and/or able to participate?

**Adoption – staff level:** Can and will those who are supposed to execute the intervention actually commit themselves? The capacity and motivation of different professional groups to engage in a given intervention, and specific work modes and tools developed for this, are regarded as crucial for the actual reach and impact of settings-based interventions. Based on the available evidence it must, as far as possible, be explored which barriers and facilitators are in play to move the professional use of effective interventions further.

1 Stakeholders are individual or collective actors having an interest in a given project and/or potentially being affected by its deliverables. In this research program focus is on internal actors interested in and/or affected by the described intervention. External stakeholders encompass all actors having a stake in the program and its delivery, without taking active part in any intervention components and activities (3).

**Implementation:** How consistently is the intervention, and its various parts, delivered? Fidelity issues of the intervention come into focus; if the intervention went as planned; what actually happened, and why; and if the effects corresponded to what was expected and intended. A further important point is to what degree the intervention is modified over time.

**Maintenance – individual and setting level:** Can a given intervention and its effects be maintained over time? This point is often decisive in connection with an overall evaluation of an intervention. In relation to the individual end user, the maintenance issue is about the ability to keep up changes in health-related habits and routines promoted by a given intervention. At the organizational level, the maintenance issue centers on, for instance, the feasibility of making the intervention part of day-to-day operations.

The table below illustrates how the RE-AIM framework will be further primed in this particular project.

| **Element Level Description Measure Assessment** | | | | | |
| --- | --- | --- | --- | --- | --- |
| **Reach**  Individual  (target population)  The impact of an  intervention on pri- mary and secondary  outcomes  CF. Information on  *Variables* and *Anal- yses of effect* for WP 1  CF. Information on  *Variables* and *Anal- yses of effect* for WP 1  Setting &  Individual (target staff)  The number and rep- The target staff and Direct observations  resentativeness of institutions are com- and e-surveys. Barri- preschools that adopt pared to the larger ers and facilitators to the intervention ‘denominator’ popu- adoption will also be  lation. assessed.  Number intervention  staff that adopt the | Individual The number and characteristics of  (target population) participants that re-  ceive, or are affected by the intervention | | | The target population Demographic infor-  is compared to the mation on nonpartici- larger ‘denominator’ pants as well as par- population. ticipants. | |
| **Efficacy**  **Adoption** |  | | | | |
|  | Program | | | | |
| **Implementation**  **Maintenance** | Setting & Individual  (target population) (target staff) | Protocol fidelity, the consistency and skill of how the various intervention compo- nents are delivered by target staff.  Satisfaction with and understanding of significant interven- tion outcomes as- sessed by the target population, together with their next of kin. | Barriers and facilita- tors reported by tar- get staff and target population and their next of kin during implementation | | Field notes and inter- views examining im- plementation issues, with target staff, reached children and their next of kin. |
|  | Setting & Individual (target staff) | Long-term effects on outcomes measures at the individual level  The extent to which the intervention be- comes institutional- ized as part of the daily routines and organizational prac- tices. | Measures the extent to which innovations become an enduring part of the behav- ioral repertoire of the preschool setting. | | Direct observations, structured interviews and e-surveys |

## Analyses of effect

Preschool staff, preschool managers and relevant parts of the municipal administration and management in Svendborg, will be identified and included in the process evaluation. Key methods will be participant observation of practice, individual and group interviews and e-surveys. The children’s perspective will be explored via observation studies and protocol-based assessments of the preschool’s social and pedagogical environments. Participant observation and go-along interviews are applied to capture the children’s experiences (4-6).

The data collection will begin in the spring of 2016 and continue simultaneously with the local implementation processes until the spring of 2019.

Perspectives

RE-AIM makes up a key component in the compiled framework on Knowledge Translation (KT) – which in health sciences is generally defined as a dynamic process that includes synthesis, exchange and application of knowledge to improve health and wellbeing and provide more effective services (7-8). The KT approach is further informed by Knowledge-to- Action (K2A) approaches developed over a number of years by the Canadian Institutes of Health Research (CIHR) (9). Together K2A and RE-AIM form a systematic and well developed methodological toolbox to support integration of best available research evidence with local context and practice and, finally, to feed back to the general knowledge base. For this particular project, it is of value to differentiate between two types of knowledge translation processes – namely *integrated and final KT.* The latter is concerned with promoting the findings, experiences and results of the research project. Key messages for communication and dissemination are developed to facilitate transfer of knowledge, targeting specific audiences. Integrated KT, also found under the headings of co-creation of knowledge and collaborative research, refers to the processes in which KT is installed as a continued activity to ensure that all project phases are based on the best available empirical and theoretical knowledge by facilitating close interaction between researchers, end users and other relevant stakeholders (9).

The basic premise is that KT should be utility-driven in the sense that knowledge generated from research (constituting one type of information) is only complete when it informs stakeholders on matters of relevance and importance, thereby assisting in the development, modification and planning of current and future interventions.

# WP 3: Motor performance and musculoskeletal disorders

### Background

Intuitively, motor skills and musculoskeletal (MSK) disorders are linked, but the reality is that a knowledge gap exists and the association between the two is unclear at present. MSK disorders are now the largest contributor to the global burden of disease (1) and the leading somatic cause of disability in Denmark (2). Research published over the last decade has consistently shown that MSK disorders start early in life (3-5), and that back pain in adolescence leads to back pain in adulthood (4). However, why and how early MSK disorders and back pain originates is unknown because, so far, studies have mainly focused on children aged 12 years or older. Importantly, the immediate consequences of poor MSK health early in life appear to be extensive. For example, children experiencing pain may miss school and withdraw from sport and other social activities and are at risk of the developing negative health behaviours such as physical inactivity, when compared to children with good MSK health. This may in turn increase the risk of lifestyle disorders later in life such as cardiovascular disease or diabetes (6, 7). In addition, appropriate use of the MSK system is likely to decrease the risk of both overuse injuries (8, 9), which appear to be relatively prevalent in younger children (10). Also, the risk of traumatic injuries might be reduced (11) and several motor control interventions have been shown to decrease the risk of traumatic injuries among adolescents and military recruits (12-14).

Surprisingly, the importance of regular motor skills training of preschool children in terms of developing MSK problems has never been investigated before. However, there is good reason to believe that improved motor performance may have a positive effect on preventing problems of MSK origin. Firstly, several studies of focused motor performance training have shown an increase in muscle control, coordination and balance in adults (15-17). In addition, several interventions designed to improve motor development in young children have been shown to be effective (18) even at three years’ follow-up (19). Secondly, motor performance training of adults has revealed improved activation of the abdominal musculature especially when challenged by sudden trunk perturbations (20, 21). This is relevant, as children with poorly developed motor abilities (Developmental Coordination Disorder) often show poor activity in these muscle groups (22). Thirdly, it is likely that motor performance training has a positive effect on the development of ‘normal’ movement patterns, resulting in appropriate functioning of mechanical joints and muscle load.

Finally, studies indicate that improved motor control can reduce the frequency of MSK injuries in the extremities (12-14).

High quality studies investigating the potential benefit of improved motor skills on MSK health are urgently needed. A prophylactic strategy focusing on improving motor skills in preschool children may potentially reduce the prevalence of current and future risk of MSK injuries and the consequences thereof.

